## 2. Clinical Evaluation Plan

The ETPR is part of an investigator-initiated clinical development plan. The objective of this clinical development plan is to establish adjunct TP use in CIED procedures. The roadmap to that goal lists several studies to address the different research questions that will have to be answered. These follow the phases set out in the IDEAL framework [13]. 

Idea (IDEAL Stage 1): Taurolidine use is common in locking solutions and recommended in the current guidelines and consensus documents [14,15,16,17,18,19]. Taurolidine solutions are used during lung transplantations [20]. Taurolidine was researched for adjunct use during dental implantation, with a focus on how it affects the buccal microbiome [21,22]. It has shown good results when used during spinal fusion surgery [23]. Taurolidine has been used in different galenic formulations to treat infections in difficult settings [24]. Life-threatening ventricular assist device driveline infections and localised major CIED infections (pocket) were salvaged via debridement using adjunct taurolidine irrigation as a method of last resort [25,26,27,28,29]. 

Development (IDEAL Stage 2a): The physicians involved developed the routine use of adjunct TP during CIED placement and elaborated the standard operating procedure outlined below and on the ETPR website (www.etpr.eu; accessed on 1 June 2023). One manufacturer conducted the preclinical testing and obtained the “Conformité Européenne” for a taurolidine solution: TauroPace™. The investigator-initiated ETPR recording adjunct TP use during CIED procedures follows consecutive cases from multiple centres in a prospective manner [Figure 1]. As the estimation of the infection rate needs to be defensible, only interventions registered prior to the procedure will be followed-up. As the rate of CIED infections is expected to be very low, this registry is a multicentric, international endeavour that will run for several years (ETPR plans to include 2300 procedures and to run until 2030; this depends on the number of centres willing to participate and the annual rate of CIED procedures with adjunct TP use in these centres). Four reports are planned. Analyses will inform the case number calculations for the future studies outlined in Stage 3. The positive reporting of safety will improve the manufacturer’s post-marketing surveillance of safety issues that might otherwise be reported by employing physicians only in clinically relevant cases.

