Exploration (IDEAL Stage 2b): A study researching the impact of adjunct TP use against a retrospective control gives a first impression of major CIED infection rates with and without TP (ClinicalTrials.gov Identifier: NCT05576194). These rates may be compared with comparative effectiveness measures from randomised controlled trials (RCTs) of other interventions used for the same purpose. The results could be used for a case number calculation for the planning of future studies. A case–control study of CIED extraction will investigate the reasons for CIED removal. Controls with similar risk factors for CIED infection undergoing CIED placement will be matched to the cases eligible for CIED hardware removal in the event of CIED infection. This is the only study with enough CIED infections to allow multivariable modelling of causation. Its results could guide the participant selection of an initial RCT in selected patients and the case number calculation of an ultimate RCT in unselected patients. 

Assessment (IDEAL Stage 3). Treatment guidelines may mention potential infection prevention with taurolidine after a first RCT of TP against the standard of care as defined in the treatment guidelines at that point in time. This may be the FederaL University of Schleswig-Holstein’s CIED Irrigation Trial (FLUSH-IT) with its comparator of no disinfection of the CIED and its components, or the Worldwide Antibiotic Stewardship in CIED Infection Prevention Trial (**WASH-IT**), which compares the intervention with adjunct TP, without preoperative intravenous antibiotic administration versus the standard of care at that point. To keep the size (and cost) of such a project reasonable, participants are selected according to their potential to benefit from the treatment, and the primary endpoint is defined to prove the direct effect. 

Long-term (IDEAL Stage 4). The ETPR begun at stage 2a will accumulate large case numbers to estimate small event rates more precisely; the plan aims to follow up on participants for years afterwards to reveal possible late effects. At the same time, results from the controlled cohort study and a matched case–control study, plus multiple interim analyses of the registry, are needed for an eventual RCT to begin. The prospective registry should therefore continue for the surveillance of established techniques (SOP from www.etpr.eu). 

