## 6. Statistical Analysis

The ETPR is designed for comparisons between the intervention with TP and historical controls, with a two-sided confidence level of 0.95. The primary estimand is the rate of patients who develop a CIED infection after a CIED procedure with adjunct TP before a repeat procedure (i.e., system modification) on that CIED is performed or the patient succumbs. This rate of infection is needed to evaluate the intervention with TP during CIED placement procedures. Exact binomial statistics will be used for CIED infection rates at 3 and at 12 months, estimated as the number of procedures followed by a CIED infection relative to the number of registered procedures with at least the respective follow-up times or an event within the specified time periods. For the first sensitivity estimand, the intercurrent events (Table 2) of generator replacement, system change, revision (i.e., any procedure that touches the CIED within the follow-up period), and death are considered to be competing risks in the estimation of the cumulative incidence curve. Event times end at these events, as these events can trigger CIED infections, but sub-distribution hazards are used to calculate the cumulative incidence function. This leads to fewer upward-biased estimates than when considering these intercurrent events as censoring the event time. Censoring is restricted to failure to follow-up (i.e., death, discontinuation) and the end of observation (i.e., system modification). Other intercurrent events, such as the intravenous administration of antibiotics (e.g., in the treatment of pneumonia), will not be considered, as in the published intention-to-treat data. Their sum is expected to be independent of TP use. This decision is taken to avoid estimates that are too low for the evaluation of the intervention.

Another objective is to gather planning data for future studies. In randomised controlled trials (RCT), the primary estimand is the cause-specific hazard ratio. This translates into censoring at the occurrence of competing risks. The second sensitivity estimand of the ETPR is the rate of major CIED infections per time survived without competing risks. 

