The confidence level will not be adjusted for multiple checks, as all analyses will be performed, and conclusions will be based on the latest results of the interim analyses or final results only. Times to major CIED infection or to death will be analysed using Kaplan–Meyer curves and cause-specific hazard ratios for the numbers of risk factors related to the patient, the CIED, or the procedure. ADE and complications will be analysed similarly using logistic regression.

The secondary estimand is all-cause mortality after CIED procedures using TP between procedures accessing the pocket. Intercurrent events are handled similarly (see Table S1 in the online supplement).

To facilitate causal inference in future research, the known risk factors for major CIED infection are reported. Their distribution should enable the calculation of propensity scores or more general balancing weights [31]. Such analyses would consider the randomness of historic controls instead of using historic results as performance goals.

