### Sample Size

The performance goals for the rate of major CIED infections vary according to country, evidence level, CIED type, and patient selection. They are expected to be higher in a revision procedure involving a complex CIED in high-risk patients than for de novo implants in otherwise healthy patients within a well-maintained setting. Additionally, the novel criteria for major CIED infection have evolved [1]. Accordingly, the published 12-month rates range from 0.7% to 4.2% (Table 3). The three-month rates are available from WRAP-IT and the Danish device registry, with values of 0.8% and 1.0% in controls, respectively [32]. For future studies researching TP use, we expect to plan for a 12-month rate of 0.5%. If its ratio to the three-month rate is 0.8/1.2, as in the WRAP-IT controls [8], then we assume a three-month rate of 0.33%.

For an approximate 95% confidence interval, to exclude a risk difference of 0.8% − 0.33% = 0.47%, when the true event rate is 0.33%, the sample size needs to exceed 572. 

For an exact 5% binomial test to have a power of 80% in detecting the difference between the hypothetical rate of 1% (0.8%) and the true rate of 0.33%, the sample size needs to be 1140 (2000).

Assuming a major CIED infection rate in the registry of 0.5% at 12 months and 0.33% at 3 months, a comparison with the performance criteria from the literature would require the sample sizes shown in Table 3.

We therefore plan to publish the ETPR results after the twelve-month follow up of 400, 900, 1420, and 2300 procedures. For the long-term evaluation, a report after the follow-up period of 36 months is planned for all procedures enrolled.

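### The reason given for not adjusting the 95% level protects the conclusion at 2300 procedures, but not the interim superiority conclusions that the plan also permits

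*Protocol article*

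**What the plan says.** Section 6 (Statistical Analysis) sets the frame: "The ETPR is designed for comparisons between the intervention with TP and historical controls, with a two-sided confidence level of 0.95". Infection rates at 3 and 12 months are to be analysed with exact binomial statistics.

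On repeated analysis it says: "The confidence level will not be adjusted for multiple checks, as all analyses will be performed, and conclusions will be based on the latest results". Read to its end, the second half of the reason is that "conclusions will be based on the latest results of the interim analyses or final results only".

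The Sample Size subsection fixes the looks: "We therefore plan to publish the ETPR results after the twelve-month follow up of 400, 900, 1420, and 2300 procedures". Section 2 agrees on their number: "Four reports are planned". Table 3 gives sample sizes for showing superiority over fixed performance goals and prints in bold the sizes chosen for reports. Among these are 391 and 1420 (goal 1.2%, WRAP-IT control), 880 (goal 1.43%, Danish registry) and 2300 (goal 1.03%, PADIT). The sizes 572 and 681 are also bold. No sentence ties a report to a single goal.

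Section 2 says that results of other studies, "plus multiple interim analyses of the registry, are needed for an eventual RCT to begin". It qualifies the target of 2300 procedures: "this depends on the number of centres willing to participate and the annual rate of CIED procedures with adjunct TP use in these centres".

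**The concern.** Performing every analysis removes selective reporting, and letting the newest result replace older ones protects the last result. Neither step limits the error of an interim conclusion while it is the newest one, and the plan's sentence expressly allows such a conclusion. Each report is published and uses the full 95% level, and the sizes come from a superiority table. The registry therefore has up to four occasions to announce superiority over a historical rate, each with its own chance of being wrong.

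At stake is what a reader of the 400, 900 or 1420 report may take from an interval that excludes a goal. An interim claim could be public, and could feed the planning of a randomised trial, before the 2300 analysis fails to support it.

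**Working it through.** **Inputs.** Looks at n = 400, 900, 1420 and 2300 (Sample Size). Two-sided 95%, so 2.5% in the direction of superiority (section 6). Goals p0 of 1.2%, 1.03% and 1.43%, with 0.7% and 0.8% at the low end (Table 3). Assumed true 12-month rate p1 = 0.5%.

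**Reproducing the plan's figures.** The limit c is the largest k with P(X ≤ k | n, p0) ≤ 0.025, and power is P(X ≤ c | n, p1).
- n = 1420, p0 = 1.2%: c = 9, power 82.1%.
- n = 2300, p0 = 1.03%: c = 14, power 81.6%.
- Approximate interval, N = 1.96² p1(1 − p1)/(p0 − p1)². For p0 = 1.2%: 3.8416 × 0.004975/0.007² = 390.0 (Table 3: 391). For p0 = 1.03%: 3.8416 × 0.004975/0.0053² = 680.4 (Table 3: 681).

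The sizes of the last two reports thus fit an exact test with 2.5% in the lower tail.

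**One goal tested at all four reports.** Set the true rate equal to the goal. Add independent binomial increments of 400, 500, 520 and 880 procedures, and count a path as a false claim the first time its cumulative count is at or below the limit.

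| Goal | Limits at 400/900/1420/2300 | Cumulative chance of a false claim | 2300 alone |
|---|---|---|---|
| 1.03% | 0/3/7/14 | 1.59%, 2.92%, 4.25%, 5.47% | 2.23% |
| 1.2% | 0/4/9/17 | 0.80%, 2.25%, 3.90%, 4.96% | 2.07% |
| 1.43% | 1/5/11/21 | 2.14%, 2.89%, 4.02%, 4.99% | 1.77% |
| 0.8% | none/1/4/10 | 0, 0.60%, 1.50%, 3.31% | 2.45% |
| 0.7% | none/1/3/8 | 0, 1.32%, 1.95%, 3.39% | 2.05% |

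For the two lowest goals, even zero infections in 400 cannot reject, so the first look adds nothing. By simulation, an interim claim that the 2300 analysis does not support occurs in 2.9% (goal 1.2%) and 3.2% (goal 1.03%) of registries.

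**Each report tests only the goal that set its size** (1.2%, 1.43%, 1.2%, 1.03%; limits 0/5/9/14). Counting only claims that are false, the chance of any is 2.2% at a true rate of 1.03%, 3.2% at 1.2% and 1.5% at 1.43%.

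**Each goal tested once, nothing tested at 400** (1.43% at 900, 1.2% at 1420, 1.03% at 2300). The same three true rates give 2.2%, 2.6% and 1.3%. Limits at 1420 and 2300 stay at 9 and 14, so power stays at 82.1% and 81.6%. At 900 the limit against 1.43% stays at 5.

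**O'Brien-Fleming-type (Lan-DeMets) spending of 2.5%.** Against 1.2% the limits are none/1/6/17 and the total error is 2.1%. Against 1.03% they are none/0/5/14 and 2.4%. The 2300 limits match the unadjusted ones, so final power stays at 95.5% and 82%. At 1420, however, the limit against 1.2% falls from 9 to 6, and P(X ≤ 6 | 1420, 0.5%) = 43% replaces 82%.

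**Sidedness.** The Sample Size text speaks of an exact 5% test. Read as 5% in the lower tail, one goal at all four reports gives 9.4% (1.03%), 11.1% (1.2%) and 8.5% (1.43%). Own-goal testing gives at most 8.4% at the three true rates, and one test per goal at most 4.8%.

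**The case against.** The plan declares its choice openly and gives a reason. It provides no stopping for efficacy; section 4.4 names only unacceptable risk or incidents as grounds for ending early. Later results replace earlier ones, so the conclusion in force at any one report has at most 2.5% error in the direction of superiority. Section 2 describes interim results as input to a randomised trial, not a substitute for one. The Sample Size text promises publication of results, not a superiority declaration each time. Table 3 also places each chosen size in the row of one goal, and on that reading the error is at most about 3.2%.

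Most of this stands. A reader might infer that the registry's final claim carries double its nominal error. The documents do not support that, because the 2300 analysis keeps its level. A reader might also infer that most false claims come from the small early reports. Against 1.2%, only 2.25 of 4.96 points (45%) arise at 400 or 900. That an interim claim may never be superseded is possible if enrolment falls short, but the enrolment proviso does not establish it.

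The objection does not remove the sentence that lets interim results carry conclusions, nor the superiority purpose of the table that supplied the report sizes. Nothing in the text restricts a report to one goal.

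**Conclusion.** The concern holds in a limited form. The stated reason justifies an unadjusted level at 2300 procedures and does not justify it for interim superiority conclusions. What rises is the chance that at least one of four published reports makes a false claim. That chance roughly doubles, to between 5.0% and 5.5% against a nominal 2.5%, if the same goal of 1.03%, 1.2% or 1.43% is tested at every report. The rise is smaller for goals of 0.7% to 0.8%, and smaller again if each report tests its own goal.

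These figures assume cumulative data, a true rate equal to the goal (or, for own-goal testing, equal to one of the three goals) and 2.5% in the lower tail. Testing several goals in one report, or both the 3- and 12-month rates, would add multiplicity that is not counted here. This is a matter of wording what each report may conclude, and it does not invalidate the design.

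**What to change.** In section 6, replace the sentence on multiple checks with a rule such as: each performance goal is tested for superiority once, at the report sized for it in Table 3 (1.43% at 900, 1.2% at 1420, 1.03% at 2300). The 400 report and all other interim comparisons give the rate with its exact 95% confidence interval as estimation only. State the sidedness in the same place.

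This costs one sentence and no extra procedures. Power is kept at 1420 and 2300 (82% each). What is given up is any superiority claim at 400, where power against 1.2% is only P(X = 0 | 400, 0.5%) = 0.995^400 = 13%, and early claims against goals assigned to a later report.

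Two alternatives are defensible if their cost is stated. Interim claims could be allowed only under O'Brien-Fleming-type spending: limits and power at 2300 are unchanged, but power at 1420 against 1.2% falls from 82% to about 43%. Or superiority could be concluded only at 2300, which defers every superiority claim to that report.

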### 4.5. Data

The registry allows for a full survey. The data model is based on the following data sources: primary center-based data collection e.g., on specific indication criteria and on the indication of the product under investigation (comorbidities). Indication criteria comprise patient-related risk factors (<65 years, male gender, renal impairment, COPD, heart failure, chronic skin disease, malignancy, immunosuppression, oral anticoagulation, dual platelet inhibition, diabetes mellitus, hematoma formation, and previous implant infection) and procedure-related risk factors (procedure duration longer than 59 min, inexperienced operator, revision, generator substitution, abandoned lead, more than two leads placed, temporary pacing, and bulkier/heavier devices: S-ICD, ICD, CRT), which are recorded. 

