## 8. Conclusions

Recently, we have learned about the practice whereby the majority of centres use irrigation solutions containing various antimicrobial substances in everyday practice in the hope of gaining the advantage in the battle against localised CIED infections [38]. However, high-quality evidence to support these measures is missing or not supportive [7,39].

The solution researched in the ETPR is the use of an adjunct during CIED placement. It has been designed to keep all CIED system components disinfected during any invasive CIED procedure. It is certified in this context. The ETPR will be fit to provide information regarding efficacy while researching the safety of the intervention with TP during CIED placement, both for the patients and the CIEDs. Eventually, the ETPR will serve as a collection of complications related to the placement of CIEDs during a maximum follow-up period of 36 months.

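### The stated covariate for time to death is a count of infection risk factors that scores age under 65 as a risk, so the secondary mortality model builds in an age effect that is probably of the wrong sign

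*Protocol article*

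**What the plan says.** Section 6 (Statistical Analysis) of the protocol article handles two outcomes in one sentence: "Times to major CIED infection or to death will be analysed" by survival curves and by "cause-specific hazard ratios for the numbers of risk factors related to the patient, the CIED, or the procedure". The covariate is thus a number of factors, and it is the same for infection and for death.

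Section 4.5 (Data) holds the only itemised list of such factors. It begins: "Indication criteria comprise patient-related risk factors (<65 years, male gender, renal impairment, COPD, heart failure", and continues to 13 patient-related items, followed by a procedure-related group that includes device type. Age under 65 is the only age item.

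Section 6 also indicates what the factors were chosen for, saying that "the known risk factors for major CIED infection are reported" to support later balancing against controls. They are described as risk factors for infection, not for death.

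Mortality has a formal role: "The secondary estimand is all-cause mortality after CIED procedures using TP between procedures accessing the pocket". The article names no separate factor set, age term or reversed age coding for the death model.

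**The concern.** For infection the count is coherent, because the article itself treats age under 65 as a risk. The difficulty comes from reusing it for death. An unweighted count gives every item the same log hazard ratio. Being under 65 then adds as much to the modelled hazard of death as renal impairment or heart failure does, and being older adds nothing.

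What is at stake is the interpretation of the mortality hazard ratios for the patient-factor count, or for any total that contains it. Those ratios would mix a group of comorbidities with an age item that probably works in the opposite direction, and their size would depend on the age mix of the registry.

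**Working it through.** **Figure to reproduce.** None. The article states no number for the mortality model.

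**Structure.** Let o be the number of the other 12 patient factors (13 − 1) and y = 1 for age under 65, otherwise 0.

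- Model as stated: h(t) = h0(t) · exp[β(o + y)]
- Model with age separate: h(t) = h0(t) · exp[βo + γy]

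The stated model is the second with γ forced to equal β. For two patients with the same o, the hazard ratio of under 65 against 65 or over is exp(β), which is also the hazard ratio per factor. If that exceeds 1, the younger patient has the higher modelled hazard whatever the data say about age. This follows from the specification and needs no simulation.

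**Inputs for the size of the bias.** Only two inputs rest on the article: the 12 other factors (section 4.5) and the three-year horizon (section 8, "during a maximum follow-up period of 36 months"). The rest are assumptions:

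- share of patients under 65: 10%, 20% or 30%
- hazard ratio of death for under 65: 0.3, 0.5 or 0.7
- true hazard ratio per other factor: 1.15 or 1.30
- prevalence of each other factor: 20%
- baseline hazard: 0.03 per year, exponential survival

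**Case A: comorbidities equally common in both age groups** (200,000 simulated patients per setting).

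| True HR per other factor | HR per factor, stated count | HR per other factor, age separate | HR for under 65, age separate |
|---|---|---|---|
| 1.15 | 1.04–1.12 | 1.14–1.15 | about 0.3–0.7 |
| 1.30 | 1.16–1.27 | 1.29–1.31 | about 0.3–0.7 |

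On the log scale:

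- True 1.30 (ln = 0.262): ln 1.16 = 0.148 and ln 1.27 = 0.239. Attenuation runs from 1 − 0.239/0.262 = 9% to 1 − 0.148/0.262 = 43%.
- True 1.15 (ln = 0.140): ln 1.04 = 0.039 and ln 1.12 = 0.113. Attenuation runs from 1 − 0.113/0.140 = 19% to 1 − 0.039/0.140 = 72%.

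With a true 1.30, the stated count therefore gives under 65 a hazard ratio of 1.16 to 1.27, where the assumed truth is 0.3 to 0.7.

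Two checks on the age assumption, again with a true 1.30: if age under 65 has no effect on death, the count gives 1.27 to 1.29. If it raises the hazard (ratio 1.2), the count gives 1.29 to 1.30 and the bias almost vanishes.

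**Case B: younger patients have fewer comorbidities.** Large-sample exponential fit with a true 1.30 per factor, 25% under 65, 11 or 12 other factors at 20–30% prevalence, and a hazard ratio for age 65 or over of 1.5 to 3 (equivalently 0.67 to 0.33 for under 65).

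| Comorbidity prevalence under 65, relative to 65 or over | HR per factor, stated count |
|---|---|
| 1.0 | 1.17–1.25 |
| 0.8 | 1.23–1.28 |
| 0.7 | 1.25–1.31 |
| 0.6 | 1.30–1.35 |

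Two errors oppose each other. The misplaced age item pulls the estimate towards 1. Leaving age unadjusted pushes it up, because the patients with more comorbidities are then also the older ones. At about 0.6 to 0.7 the two roughly cancel. The sign of the age contribution is not repaired by this, since exp(β) still exceeds 1.

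**The case against.** **The link is inferred.** Section 6 does not cite section 4.5. It names three groups of factors where section 4.5 names two, and a condensed article may leave the factor set for a secondary model to the full protocol, which the Data Availability statement offers on request. This stands as a caveat. It does not remove the point, because the article does fix the covariate for death as a number of risk factors, contains only one list, and gives no other treatment of age.

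**Little rests on this model.** The secondary estimand is all-cause mortality itself, which covariates do not alter. A reader might infer that patients would be ranked wrongly by risk of death. The article plans no prognostic score, ranking or decision based on mortality risk, so that reading goes too far.

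**The bias may be absent.** A reader might also infer that the mortality hazard ratios are bound to be distorted. The article gives no age mix, mortality rate or age effect, and case B shows that the bias in the ratio per factor can be small, nil or reversed. This objection stands in full against any single figure for the bias.

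**Other items were not chosen for mortality either.** Male gender, chronic skin disease and previous implant infection are examples, and an unweighted count is a deliberate simplification. That is fair. Age differs in that its direction is expected to reverse between the two outcomes, so it is more than a matter of imprecise weighting.

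**Conclusion.** The point holds in a limited form. If the section 4.5 list is what section 6 counts, the secondary mortality model must give a patient under 65 a higher hazard of death than an otherwise identical older patient whenever the ratio per patient factor exceeds 1. Calling that sign wrong rests on the general assumption that mortality rises with age, which the article does not state.

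The bias in the ratio per factor is possible but not established. It ranges from clear attenuation when comorbidity does not vary with age to none, or a slight excess, when younger patients have clearly fewer comorbidities, and every one of these figures depends on assumed inputs.

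The effect is confined to the mortality hazard ratios for the patient-factor count or a total that includes it. The exact binomial infection rates, the overall mortality estimate, the comparisons with performance goals, the sample sizes and the use of the count for infection are untouched. It is a worthwhile correction to a secondary analysis and does not threaten the main results.

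**What to change.** Add one sentence to the Statistical Analysis section. For time to death only, the patient-factor count omits age under 65, and age enters as its own term: continuous if exact age is recorded, otherwise as the under-65 indicator. The article shows only the indicator, so the availability of exact age needs checking; the indicator alone is enough to free the sign. Keep age under 65 in the count for the infection model. The same sentence can confirm that the counted factors are those listed in section 4.5.

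The cost is one extra parameter in the mortality model and a count defined differently for the two outcomes, which reports should state so that the two ratios per factor are not compared as if they were alike.

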## 3. Scope

In addition to the scope of generating feasibility data according to the clinical evaluation plan outlined above:

The ETPR should define and develop patient-, CIED- and procedure-specific understandings of factors driving complications related to the placement of CIEDs in Europe.

The ETPR may shape the development of guidance on how to reach and retain the best possible practice in CIED placement in different settings and countries across Europe.

The ETPR will develop and evaluate a set of suitable tools, solutions, and strategies applicable to the placement of different types of CIEDs with the adjunct use of a new medical device containing taurolidine.

The ETPR will build new site capabilities and develop training activities to increase the number of contributing sites and expand the pool of investigators, including investigators from under-represented communities and naïve investigators in geographies where the study infrastructure may be insufficient.

Ultimately, the ETPR will gain planning data related to the feasibility of conducting future RCTs researching the safety, clinical effectiveness, and cost-effectiveness of adjunct TauroPace^TM^ use against current standard of care in patients eligible to undergo any CIED procedure with the placement of any CIED.

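### Infection hazard ratios for risk-factor counts carry no minimum event number, although the first two reports expect only about 2 and 4.5 infections

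*Protocol article*

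**What the plan says.** The paragraph on time-to-event analysis in Section 6 begins "Times to major CIED infection or to death will be analysed using" and goes on to name Kaplan–Meier curves and "cause-specific hazard ratios for the numbers of risk factors related to the patient, the CIED, or the procedure". The same paragraph explains that the confidence level is not adjusted for repeated looks, because every analysis will be carried out and conclusions will rest on the most recent interim or final results. It attaches no minimum event number to the hazard ratios, and does not say whether the counts enter one model or several.

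The Sample Size section gives the planning rate ("we expect to plan for a 12-month rate of 0.5" per cent) and the timing: "We therefore plan to publish the ETPR results after the twelve-month follow up of 400, 900, 1420, and 2300 procedures". For the longer term, "a report after the follow-up period of 36 months is planned for all procedures enrolled".

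Two other places bear on the point. Of the separate case-control study, Section 2 (IDEAL Stage 2b) says: "This is the only study with enough CIED infections to allow multivariable modelling of causation". Section 3 sets a wider aim for the registry: "The ETPR should define and develop patient-, CIED- and procedure-specific understandings of factors driving complications".

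**The concern.** The report sizes come from comparing a single infection rate with fixed performance goals. They were not chosen to support a regression, and the assumed rate is low enough that the early reports will hold only a handful of infections.

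The Cox partial likelihood has one term per event. With no infection there is nothing to estimate. With one or two, an estimate can run off to infinity, for example when every infected patient sits at the extreme of a count. When a finite estimate exists, its sign can easily be wrong.

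Because conclusions rest on the latest available report, a hazard ratio published at 400 procedures would stand until the 900-procedure report replaces it. Readers could be shown a real risk factor as apparently protective. Section 6 also sits awkwardly with the article's own statement about which study has enough infections for such modelling.

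**Working it through.** **Inputs from the article.** The true 12-month rate is 0.5% and the 3-month rate 0.33%. Reports come at 400, 900, 1420 and 2300 procedures (Sample Size, Table 3). The confidence level is 95%, two-sided (Section 6).

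**1. Reproducing the plan's figures.** For the approximate interval, N = 1.96² × p(1 − p) / (p0 − p)².
- 0.33% against 0.8%: 3.8415 × 0.0033 × 0.9967 / 0.0047² = 572, as stated.
- 0.5% against 1.2%: 3.8415 × 0.005 × 0.995 / 0.007² = 390.03, so 391, as in Table 3.
- 0.5% against 1.03%: the same numerator over 0.0053² = 680.4, so 681, as in Table 3.

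The rates are therefore read as the plan intends. The article gives no event count or precision for the hazard ratios, so there is no stated figure to reproduce for them.

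**2. Infections per report.** Expected number = 0.005 × N; P(none) = 0.995^N; the last two columns are binomial.

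| Procedures | Expected infections | P(none) | P(at most 2) |
|---|---|---|---|
| 400 | 2.0 | 13.5% | 68% |
| 900 | 4.5 | 1.1% | 17% |
| 1420 | 7.1 | 0.08% | 2.7% |
| 2300 | 11.5 | 0.001% | 0.08% |

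**3. Information in closed form.** For one factor present in half of the procedures, the hazard ratio detectable with 80% power is exp(2.8 / √(0.25 × events)), where 2.8 = 1.96 + 0.84. This gives about 52, 14, 8.2 and 5.2 at the four reports.

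**4. Simulated joint fit of three counts.** The article gives neither the effect per factor nor the distribution of the counts, so these are assumptions. The true hazard ratio is 1.3, 1.5 or 2.0 per added factor, and the mean 12-month risk is 0.5%.
- Wide spread: patient count Bin(13, 0.23), CIED count Bin(2, 0.35), procedure count Bin(6, 0.2).
- Narrow spread: Bin(13, 0.12), Bernoulli(0.4), Bin(6, 0.1).
- Runs: 500, 300, 250 and 200 at the four sizes.
- Not estimable means no events, |log HR| > 5, or a standard error above 10.

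Each cell shows per cent of runs, wide / narrow spread.

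| Procedures | Not estimable: HR 1.3 | HR 1.5 | HR 2.0 | Not estimable, or at least one HR below 1: HR 1.3 | HR 1.5 | HR 2.0 |
|---|---|---|---|---|---|---|
| 400 | 37.6 / 66.2 | 33.0 / 60.6 | 37.6 / 64.4 | 84.0 / 89.8 | 77.6 / 83.8 | 59.6 / 80.4 |
| 900 | 3.3 / 21.7 | 10.0 / 22.3 | 8.3 / 20.3 | 68.0 / 75.7 | 52.3 / 66.0 | 32.7 / 50.0 |
| 1420 | 1.2 / 7.2 | 1.2 / 4.4 | 0.8 / 6.4 | 58.4 / 65.6 | 35.6 / 52.8 | 18.4 / 38.4 |
| 2300 | 0 / 0 | 0 / 2.0 | 0 / 0.5 | 47.5 / 59.0 | 23.0 / 42.5 | 5.5 / 20.0 |

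**5. Counts fitted separately.** With Bin(11, 0.24), Bernoulli(0.4) and Bin(6, 0.2) and a true hazard ratio of 1.5, failure at 400 was 11% for the patient count, 16% for the procedure count and 58% for the binary CIED count. A second check put the patient and procedure counts at 13–23%. (No true failure rate can lie below the 13.5% chance of no infection, so the 11% is simulation error.) At 900 the figures were 1%, 1% and 18%. At 2300 all were under 1%, with a wrong sign in 2% (patient), 9% (procedure) and 20% (CIED).

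**6. The 36-month report.** The article assumes no 36-month rate for the registry. If it were three times the 12-month rate, as 2.1% is to 0.7% in the Introduction, then 2300 × 0.015 = 34.5 infections are expected. Under the wide spread, each coefficient then has the wrong sign in about 6% (HR 1.3) or 2% (HR 1.5) of runs.

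**The case against.** The joint model is not in the text. Section 6 does not say joint or separate, and Section 4.5 lists only patient- and procedure-related factors, with device type under procedure, so even three counts is a reading. Taken together with Section 2, the sentence could mean simple one-at-a-time hazard ratios. Step 5 shows that failures then drop sharply for the patient and procedure counts, and that an assumed binary CIED count drives most of the trouble. This stands, and it limits the size of the claim. It does not remove the point at 400, where even separate fits fail at least as often as no infection occurs and two or fewer infections are expected in 68% of reports.

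Later reports supersede earlier ones, confidence intervals display imprecision, and the 36-month report will have more events. All true, and a reason to keep the analysis there. Carrying it out at each report is itself an inference from Section 6, though a natural one. Partly followed procedures may add a few events.

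The aim in Section 3 concerns complications, not infection alone. The Introduction puts complications at around ten per cent, and Section 6 analyses them by logistic regression. That aim is not undermined by the infection counts, nor is the planned reporting of risk-factor distributions for later balancing weights.

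A reader might also infer that centres enrolling only high-risk patients bias the hazard ratio. The calculated shift (1.42 to 1.68 against a true 1.50) rests on an assumed 20% share and assumed baseline hazards, and Section 7 already discloses the selection. It does not carry the point.

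**Conclusion.** The concern holds in a limited form. The event counts follow directly from the plan's own rate and report sizes, no event minimum is set, and Section 2 supplies the contrary statement. For a joint fit, failure to obtain a finite estimate is a real risk at 400 (about one third to two thirds of runs) and a lesser one at 900 (3–22%).

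A reader might go further and infer that the hazard ratios are often not estimable at every report. The figures do not support that: at 1420 and 2300 the failure rate is about 0–7%. What remains there is imprecision and, for modest effects, a wrong sign. At 2300 the chance that at least one of three ratios is below 1 or not estimable runs from 5.5% to 59%, depending on effect sizes and count distributions that the article does not give.

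The primary binomial rate is untouched, and the infection counts say nothing about the hazard ratios for death. This is a cheap improvement to a supporting analysis, not a flaw in the main result.

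**What to change.** In Section 6, for the infection outcome only:
- At the 400, 900 and 1420 reports, give no infection hazard ratios. Show the number of infections by risk group with exact binomial intervals.
- At the 2300 and 36-month reports, fit the hazard ratios by Firth-penalised partial likelihood with profile-likelihood intervals, and label them exploratory, in line with Section 2.
- Leave the analysis of time to death as planned.

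Penalisation keeps estimates finite once there is at least one infection. It gives nothing when there are none, and it does not make up for missing events, hence the exploratory label.

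Two optional sensitivity analyses are a single total score of pre-procedure risk factors, and a baseline hazard stratified by centre type (all-comer or high-risk-only). The total score gains stability by assuming an equal effect for each factor, which is a trade-off, so it should not be mandatory. If used, it should leave out items known only during or after the procedure: Section 4.5 lists procedure duration and hematoma as risk factors, while Table 2 treats pocket hematoma as an intercurrent event.

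The cost is a few sentences and standard software. The downside is that the three early reports carry no infection hazard ratios.
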